### Adverse drug event monitoring

Adverse events (AEs), including serious AEs (SAEs), are closely monitored and recorded on the electronic case report form throughout the duration of the trial, in accordance with Good Clinical Practice guidelines and all applicable regulatory requirements. At each study visit, participants are evaluated for AEs and asked about any symptoms that have occurred between study visits. Participants are advised and requested to report symptoms suggestive of AEs. An AE is defined as any unfavourable or unintended medical occurrence in any participant who has received the trial drug or usual care, regardless of whether it has a causal relationship with the intervention. SAE is defined as any event that (1) results in death; (2) is life-threatening; (3) requires hospitalisation or prolongation of existing hospitalisation; (4) leads to persistent or significant disability or incapacity or (5) constitutes a congenital anomaly/birth defect. AEs are documented according to the severity, duration, grade, relationship to trial drugs, interventions given and outcome. The costs of treating all adverse drug events related to trial drugs will be borne by the trial. Each AE/SAE is assessed by the site investigator for severity, expectedness and its relationship to the trial drug or study procedure (unrelated, unlikely related, possibly related, probably related or definitely related). All SAEs are reported to the Principal Investigator, who will, in turn, notify the trial sponsor and the Institutional Review Board/ethics committee in accordance with local regulatory requirements. Any serious, unexpected adverse drug reactions will also be reported promptly to the national drug regulatory authority in line with pharmacovigilance requirements. All study participants with AEs are managed and followed up until the resolution or stabilisation of the AE. Where necessary, additional medical information is obtained to ensure a comprehensive evaluation of the AE. Safety oversight during the trial is provided by a Data and Safety Monitoring Board (DSMB) and other independent safety monitors.

### Primary outcome

The primary clinical outcome is the incidence of maternal sepsis within 6 weeks (42 days) after birth.

Definition of primary clinical outcome: maternal sepsis is defined by the WHO as a life-threatening condition with organ dysfunction resulting from suspected or confirmed infection during pregnancy, childbirth, postabortion or the postpartum period. The WHO definition is used to define maternal sepsis as a suspected or confirmed infection based on table 1.

**Table 1 T1:** Definition of maternal sepsis

Symptoms/signs	Definitions
Fever	>38°C
Hypothermia	<36°C
Plus, one or more signs of mild-to-moderate organ dysfunction, including:	
Tachycardia	≥110 beats per minute
Low blood pressure	<90/50 mm Hg
Tachypnoea	≥24 breaths per minute
Altered mental status	Altered consciousness, which may include coma, disorientation, etc.
Reduced urinary output	<500 mL/24 hours or<20 cc/hour (over several hours)

### Secondary clinical outcomes

Incidence of culture-confirmed maternal sepsis within 6 weeks of birth, defined as a positive blood culture in the presence of suspected maternal sepsis.Incidence of specific maternal infection, defined as a positive microbiological culture from specific sites, including bacterial vaginosis, chorioamnionitis, endometritis, abdominal or pelvic abscess, mastitis or breast abscess, pneumonia or pyelonephritis (table 2).Number of new prescriptions of antibiotics for a specific maternal infection after enrolment, for any reason, including bacterial vaginosis, chorioamnionitis, endometritis, abdominal or pelvic abscess, mastitis or breast abscess, pneumonia or pyelonephritis (table 2).Number of new prescriptions of antibiotics for any reason (use of subsequent maternal antibiotic therapy after randomisation up to 6 weeks for any reason).Incidence of neonatal sepsis within 28 days of birth, defined as proven or possible serious bacterial infection (PSBI) or pneumonia or meningitis. PSBI is determined using WHO criteria of severe chest in-drawing, fever, hypothermia, no movement at all or movement only on stimulation, feeding poorly or not feeding at all and/or convulsions.^46^ Clinical and laboratory signs of neonatal infection will also be considered for diagnosis, for example, eye infection, skin infection, omphalitis, urinary tract infection or respiratory rate ≥60 breaths per minute.Incidence of stillbirth is defined as the birth of a baby with no signs of life at or after 24 weeks of gestation.Incidence of neonatal death (death within 28 days of birth).Duration of initial hospital stay for neonate, defined as the time from birth until the time of hospital discharge.Duration of hospital stay for the mother, defined as the time from enrolment until discharge (in days).Incidence of maternal readmission, or admission to a special care unit, for any other condition within 6 weeks of birth.Incidence of neonatal readmission, or admission to a special care unit, for any other condition within 28 days of birth.Incidence of adverse drug events (fainting or dizziness, nausea, vomiting, diarrhoea and dyspepsia) and other reported side effects.Incidence of secondary postpartum haemorrhage, defined as excessive bleeding requiring intervention (such as surgical intervention or blood transfusion) from 24 hours after birth until 6 weeks post partum.

**Table 2 T2:** Specified infections considered for maternal sepsis diagnosis

Type of infection	Description
Chorioamnionitis	Fever (>38°C) in addition to one or more of the following: fetal tachycardia≥160 beat s per minute, maternal tachycardia>100 beats per minute, tender uterus between contractions or purulent/foul-smelling discharge from the uterus prior to delivery.
Endometritis	Fever (>38°C) in addition to one or more of maternal tachycardia>100 beats per minute, tender uterine fundus or purulent/foul-smelling discharge from the uterus after delivery.
Wound infection	Purulent infection (superficial or deep infection, including necrotising fasciitis) of a perineal or caesarean wound with or without fever. In the absence of purulence, a wound infection requires the presence of fever (>38°C) and at least one of the following signs of local infection: pain or tenderness, swelling, heat or redness around the incision/laceration.
Abdominopelvic abscess	Evidence of pus in the abdomen or pelvis noted during open surgery, interventional aspiration or abscess imaging.
Pneumonia	Fever (>38°C) and clinical symptoms suggestive of lung infection, including cough and/or tachypnoea (>24 breaths per minute) or radiological confirmation.
Pyelonephritis	Fever (>38°C) and one or more of the following: urinalysis/dip suggestive of infection, costovertebral angle tenderness or confirmatory urine culture.
Mastitis/breast abscess	Fever (>38°C) and one or more of the following: breast pain; swelling; warmth; redness, abscess or infection or purulent drainage.

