##### Participant inclusion criteria

Pregnant women with a live or stillborn singleton or twin pregnancy of at least 24+0 weeks’ gestation in the active phase of the first stage of labour (cervical dilatation of 4 cm or more) or the early (non-pushing) phase of the second stage of labour.Pregnant women admitted in labour to the selected health facilities following spontaneous or induced labour with a planned vaginal birth.

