##### Participant exclusion criteria

Pregnant women of gestational age <24 weeks.Pregnant women who are not admitted to the facility with a plan to deliver vaginally.Pregnant women in threatened preterm labour with no immediate plan for birth.Pregnant women with a fever >38°C.Pregnant women with a history of use of a macrolide antibiotic in the previous 3 days.Pregnant women with a known allergy to AZM, its excipients or other macrolide antibiotics.Pregnant women with a known history of cardiac disease (such as cardiac arrhythmia or cardiomyopathy).Pregnant women with a planned caesarean birth.

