### Sample size

A sample size of 5040 (2520 in each group) is required to detect a 50% reduction in the maternal sepsis incidence rate from 6.5% to 3.25% due to AZM, at 90% power and a 5% level of significance. The sample size accounted for an intraclass correlation (ICC) of 0.011 and 20% loss-to-follow-up. The incidence rate of sepsis or severe systemic infection was found to be 6.5% in a study of maternal near-misses at the University of Port Harcourt, Rivers State, Nigeria.^47^ In a randomised clinical trial (RCT) of AZM versus placebo in Burkina Faso and The Gambia, the OR of maternal sepsis was 0.62 for any maternal sepsis and ~0.00 for bacterially confirmed sepsis.^25^ The incidence of sepsis in this study was much lower than in our setting (0.2% vs 6.5%). The ICC was derived from an analysis of the WHO Global Survey on Maternal and Perinatal Health.^48^ We require 48 health facilities and estimate each will enrol approximately 105 participants per facility within 10–12 months on average.

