### Randomisation

Sites were randomly assigned in a 1:1 ratio to either the intervention group or the control group. Randomisation was based on a minimisation algorithm that considered the state, facility level (primary, secondary and tertiary) and empirical postpartum use of antibiotics. Randomisation was undertaken by the statisticians, and the health facilities were informed of their random allocation before any participants were assessed for eligibility.

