### Data collection

Study participants are enrolled in labour and followed up with visits at 3 days, 2 weeks, 4 weeks and 6 weeks postpartum (table 3). To minimise missed visits and loss to follow-up, counselling sessions are extended to partners and family members when necessary and during follow-up visits. Reminders for follow-up appointments are sent via short message service and telephone. The details of participants’ home addresses are also collected at enrolment and updated during each visit. For participants who cannot be reached, community tracking will be done (a home-based monitoring system designed to locate participants in their homes). Consent for home visits and community tracking is obtained at enrolment.

**Table 3 T3:** Schedule of activity

Study epoch	Antenatal	Labour	Postpartum				
Visit number	0	1a	1b	2	3	4	5
Time in study	ANC visits	During labour	After delivery, before discharge	3 days	2 weeks	4 weeks	6 weeks
Assessment window/study procedure			+12 hours	±1 day	±3 days	±5 days	±7 days
Awareness and sensitisation	X						
Counselling and provision of participant’s information leaflet	X	X					
Screening for eligibility		X					
Informed consent		X					
Assign study ID number		X					
Study intervention (AZM or usual care)		X					
Vital signs		X	X	X	X	X	X
Clinical lab evaluation*		X	X	X	X	X	X
Baseline information (mother) (sociodemographic, clinical, medical history, labour and delivery information, etc)		X	X				
Baseline newborn information (sex, birth weight, birth outcome, complications, etc)			X				
Maternal outcomes		X	X	X	X	X	X
Neonatal outcomes			X	X	X	X	X
AEs		X	X	X	X	X	X
Cost-effectiveness information		X	X	X	X	X	X
Participant EOS							X

Participants who booked for ANC will be counselled/consented during the antenatal period and consented/reconsented in labour.

* Clinical lab evaluation includes full blood count; electrolyte, urea and creatinine; procalcitonin; malaria parasite and microbiology culture as indicated.

AE, adverse event; ANC, antenatal care; AZM, azithromycin; EOS, end of study.

REDCap (Research Electronic Data Capture V.13.8.3, Vanderbilt University, Nashville, Tennessee, USA) is used to collect all relevant study data. Designated investigators and study staff will enter trial data using password-protected electronic devices. Outcome data are collected during labour and childbirth and up to 42 days postpartum. Baseline sociodemographic data are also collected.

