### Statistical methods and analysis

All analyses will be intention-to-treat unless specified. Categorical variables will be summarised as frequencies and percentages. Continuous variables will be presented with N (number of observations), means (SD) and/or medians (IQRs), depending on whether they are normally distributed. The primary outcome will be analysed using a random effects logistic regression model to estimate the treatment effect with 95% CI. The model will be adjusted for the stratification variables, along with any imbalance in key baseline variables. The secondary outcomes will be analysed using random-effects models depending on the distribution of the outcome. Missing data will be described explicitly with the number reported for each variable, and where appropriate, multiple imputation methods may be employed. An interim analysis will be conducted at the halfway point through the trial (50% of the target sample with the primary outcome). If the p value indicates an overwhelming effect (as evidenced by a p value less than 0.001—the Haybittle-Peto rule),^49^ the DSMB may request unblinding, and a recommendation to stop the trial may be considered.

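### The stillbirth outcome counts fetuses already dead at enrolment, which pulls its ratio towards 1; it should be restricted to fetuses alive at entry

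*Protocol article*

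**What the plan says.** Under Participant inclusion criteria, the protocol article accepts "Pregnant women with a live or stillborn singleton or twin pregnancy of at least 24+0" weeks, in the active first stage or the early second stage of labour. The baby is undelivered at that point, so the reference to a stillborn pregnancy can only mean a fetus that has already died.

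Under Participant exclusion criteria, the only gestational limit is "Pregnant women of gestational age <24 weeks". Nothing there removes women with a fetal death.

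Data collection fixes the timing: "Study participants are enrolled in labour and followed up with visits at 3 days, 2 weeks, 4 weeks and 6 weeks postpartum". Treatment is given in labour, after consent.

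Secondary clinical outcomes then states: "Incidence of stillbirth is defined as the birth of a baby with no signs of life at or after 24 weeks of gestation". It does not require the fetus to have been alive at enrolment.

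Statistical methods and analysis adds "All analyses will be intention-to-treat unless specified" and names no restricted set for this outcome. Randomisation records that "the health facilities were informed of their random allocation before any participants were assessed for eligibility".

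**The concern.** A fetus that is dead before the woman enters the trial is a baseline characteristic. Under the stated definition it becomes an outcome event with certainty, whatever the woman receives. Such events add equally to both arms if they are balanced, so any effect on the fetuses that treatment could influence looks smaller on the ratio scale. This works in both directions. The first objective covers safety as well as effectiveness, and an increase in stillbirth would be masked in the same way as a reduction.

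The second issue is balance. Allocation is by facility, it is open, and it was known before women were screened. The minimisation factors are state, facility level and postpartum antibiotic use. If the arms happened to enrol different numbers of women with a known fetal death, the difference would enter the stillbirth comparison directly.

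**Working it through.** **1. The plan's own figure.** The article gives no figure for stillbirth. Its only calculation is for maternal sepsis: "A sample size of 5040 (2520 in each group) is required to detect a 50% reduction", "from 6.5% to 3.25% due to AZM, at 90% power and a 5% level of significance", with an ICC of 0.011, 20% loss and 48 facilities of about 105 women. Two-sided testing is assumed.

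- Two proportions, pooled variance, 6.5% v 3.25%: 921 per arm.
- Design effect: 1 + (105 − 1) × 0.011 = 2.144.
- 921 × 2.144 = 1975 per arm; 1975 / 0.80 = 2469 per arm, 2.0% below 2520.
- By clusters: 1975 / 105 = 18.8; 18.8 / 0.80 = 23.5, rounded up to 24; 24 × 105 = 2520.

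The sample size reproduces. It rests on sepsis in the mother, so the stillbirth definition does not touch it.

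**2. Dilution of the ratio.** Let *f* be the share of control-arm stillbirths in which the fetus was dead at enrolment, with equal numbers of prior deaths per arm. Let RR be the true risk ratio among fetuses alive at entry. Then

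observed RR = *f* + (1 − *f*) × RR.

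The article gives neither *f* nor an expected effect on stillbirth, so both are assumptions:

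| *f* | true RR 0.70 | true RR 0.80 | true RR 1.50 |
|---|---|---|---|
| 30% | 0.30 + 0.70 × 0.70 = 0.79 | 0.86 | 1.35 |
| 50% | 0.50 + 0.50 × 0.70 = 0.85 | 0.90 | 1.25 |
| 70% | 0.70 + 0.30 × 0.70 = 0.91 | 0.94 | 1.15 |

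At *f* = 10% a true 0.70 appears as 0.73. Restriction to fetuses alive at entry returns the true value in every row.

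**3. The absolute difference.** Assume 3% stillbirth in the control arm, *f* = 50% and RR 0.70.

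- All births: control 1.50% + 1.50% = 3.00%; intervention 1.50% + 1.05% = 2.55%; difference 0.45 percentage points.
- Alive at entry: 1.50 / 98.5 = 1.52% v 1.05 / 98.5 = 1.07%; difference 0.46 percentage points.

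The same deaths are averted, so the absolute difference hardly moves.

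**4. What an imbalance would do.** With the same assumed 3%, 2520 women (counted as one birth each) give about 76 stillbirths per arm. If one arm enrolled 20 more women with a prior fetal death, and treatment did nothing, the ratio would be 96 / 76 = 1.26. This shows sensitivity only; the number 20 is hypothetical.

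**5. Power.** With 3% stillbirth, *f* = 50%, RR 0.70, 2520 per arm and the design effect of 2.144 borrowed from the sepsis calculation, power is about 10% for all births and about 16% for fetuses alive at entry.

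**The case against.** The best counter-argument is that the article defines the event and not the denominator. The neonatal outcomes in the same list also name no at-risk set, and nobody would count a stillborn baby as at risk of neonatal death. A condensed article may leave such sets to the full protocol or analysis plan, and its intention-to-treat sentence allows exceptions. This stands in part. For the neonatal outcomes, common sense supplies the restriction. For stillbirth it does not: the wording given includes a fetus dead at entry, and the eligibility text deliberately admits such women.

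The next argument is that the impact is small. It is one of many secondary outcomes, the size of the dilution is assumed throughout, and power is low with or without the change. All of that is correct and limits the weight of the point. What restriction gains is an interpretable estimate, not an adequately powered one.

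Three stronger readings are tempting and are not supported:

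- A reader might infer that the comparison is confounded by case mix. Open cluster allocation makes that possible, but minimisation used state and facility level, and nothing in the document shows differential enrolment of fetal deaths. Nor would the planned adjustment for baseline imbalance fully answer it if it did occur. That adjustment is stated for the primary model, and prior fetal death determines this outcome completely, so restriction is the suitable remedy.
- A reader might infer that treatment effects are diluted on every scale. With balanced arms, only the ratio is affected.
- A reader might infer that fetal status at entry must already be on file because eligibility depends on it. Eligibility accepts live and dead fetuses alike, so it does not depend on it. The schedule of activity lists labour information at the labour visit but does not name fetal viability.

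**Conclusion.** The definition as written counts deaths that precede treatment, and nothing elsewhere in the article corrects it. With equal numbers of prior deaths per arm, a true risk ratio of 0.70 appears as 0.79 to 0.91 when 30% to 70% of control-arm stillbirths precede enrolment. If those percentages are read as shares of stillbirths in both arms together, the values are about 0.78, 0.84 and 0.90. The secondary analysis is to use random-effects models; for an outcome this infrequent, an odds ratio would behave in much the same way. A shift from unequal enrolment is a possibility and not a demonstrated fault. The point concerns one secondary outcome and leaves the trial's main conclusion intact, but it should be corrected because the correction is simple and the uncorrected ratio cannot be read as an effect of treatment on fetuses at risk.

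**What to change.** Before unblinding:

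- Define the stillbirth outcome as birth without signs of life, at or after 24 weeks, among fetuses alive at enrolment. Take fetal status from the record of the labour visit (1a), and apply the condition to each twin separately.
- Report fetal death before enrolment by arm as a baseline variable, so that any imbalance is visible.
- Report all stillbirths descriptively alongside.
- Keep women with a prior fetal death in all maternal outcomes, including the primary outcome.
- State live births as the denominator for the neonatal outcomes.

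Eligibility and treatment do not change. The statistical cost is a slightly smaller denominator. The practical cost depends on the data. Enrolment began in March 2025 and was projected to end by March 2026, so the sponsor must confirm that fetal status at entry was recorded, or can be retrieved from labour records, for women already enrolled. If it is missing for some, the number should be reported by arm and the result shown with those fetuses counted as alive and then as dead at entry.

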### Sample size

A sample size of 5040 (2520 in each group) is required to detect a 50% reduction in the maternal sepsis incidence rate from 6.5% to 3.25% due to AZM, at 90% power and a 5% level of significance. The sample size accounted for an intraclass correlation (ICC) of 0.011 and 20% loss-to-follow-up. The incidence rate of sepsis or severe systemic infection was found to be 6.5% in a study of maternal near-misses at the University of Port Harcourt, Rivers State, Nigeria.^47^ In a randomised clinical trial (RCT) of AZM versus placebo in Burkina Faso and The Gambia, the OR of maternal sepsis was 0.62 for any maternal sepsis and ~0.00 for bacterially confirmed sepsis.^25^ The incidence of sepsis in this study was much lower than in our setting (0.2% vs 6.5%). The ICC was derived from an analysis of the WHO Global Survey on Maternal and Perinatal Health.^48^ We require 48 health facilities and estimate each will enrol approximately 105 participants per facility within 10–12 months on average.

### Recruitment

All pregnant women will be approached during routine antenatal care (ANC) visits and on admission during labour by trained research staff who will provide study information and discuss participation. Study information will be provided and discussed using multiple formats, including videos, fliers, banners, participant information leaflets and eligibility assessment cue cards. To aid understanding, short information videos will be shown to potential participants during antenatal classes and/or after admission to the labour ward for childbirth. At the study sites, pregnant women admitted in the active phase of labour will be screened for eligibility to participate in the trial, and written consent will be obtained intrapartum from eligible participants before the onset of the pushing phase of labour. The informed consent form was translated into Hausa, Igbo, Yoruba and Pidgin English, the most popular languages used in the participating facilities.

